#### Outcomes {12}

The main end-points will be:
‘Rate of healing’ based on two observations per week of ulcer size censored at 42 days (cm^2^ per unit time). We will estimate the effect of the intervention on the change in the ulcer size per unit time, i.e. the rate of healing (see Statistical Analysis).Time to complete re-epithelialization (right-censored at 42 days).

Both end-points will be analysed with and without adjustment for baseline characteristics (trial ulcer area and participants’ age), but we prefer unadjusted outcomes in randomised studies and therefore declare them as ‘primary’.

Secondary end-points:
Rate of healing based on two observations per week up to 70 days (cm^2^ per unit time) (calculated as described below).Time to complete re-epithelisation (observed up to 70 days).Generic quality of life (QoL) measured at first dressing change, fortnightly during in-patient stay and at 6-month follow-up, using the EQ-5D 3L. This scale has previously been used and validated in a Nepali population [17]. As far as we are aware, there is no valuation tariff in the Nepalese population, although this may change by the time that the analysis starts. Therefore, we propose not to prespecify the tariff but instead select the tariff at a later date. We note that tariffs are currently available for nearby countries including Sri Lanka [18] and China [19, 20].Longer-term outcomes measured at 6-month follow-up from randomisation will be proportion with:
i.Recurrence of treated ulcer;ii.Appearance of new ulcer;iii.Anatomical changes in the limb;Days hospitalised prior to discharge and total (to include any readmission due to leprosy/ulcers) by 6 months.Health economic information:
i.Number of visits to any healthcare facility from discharge to the end of follow-up at 6 months.ii.Data on the time taken to change dressings at the twice weekly changes.

Rate of healing will be assessed from blindly assessed photographs (Fig. 2). However, as complete healing may trigger discharge, we will monitor for cases discharged before the blinded assessor in Birmingham has noted complete re-epithelization.

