### Trial design {8}

A single-centre, prospective, single blinded, parallel group, 1:1 individually randomised controlled trial. Study duration is 48 months (maximum). Participants and practitioners will not be blinded, but the assessors will be completely blinded, as we describe in the section on ulcer measurements. Each participant will be followed up for up to 6 months from the point of randomisation. Consent (see ethics) and baseline data collection will precede randomisation. A summary of the study pathway is shown in Fig. 1.

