### Intervention

#### Intervention description {11a}

The intervention uses the participant’s own blood to prepare strips of leukocyte and platelet-rich fibrin matrix (L-PRF) to be applied to the ulcer bed. The process is described in detail elsewhere [16] but briefly, up to 80ml of participants’ blood will be collected twice per week at the time of dressing change. The blood will be centrifuged to obtain the fibrin matrix gel, which will be compressed and applied to the ulcer bed and then covered with a Vaseline gauge dressing. Blood collection from participants, centrifugation procedure and application of L-PRF will be done in a minor operating room following aseptic technique. All participants (including those in the control group) will be given iron and folic acid tablets. Both control and intervention groups will receive routine twice-weekly dressing changes by trained nurses or paramedics until their ulcers are healed (complete re-epithelization) up to a maximum of 70 days. Any missed dressing change sessions will be noted but not treated as a deviation from the protocol.

In the event that a participant has more than one ulcer, the largest ulcer will be selected as the index ulcer for analysis purposes before randomisation. However, all of the participant’s ulcers will receive the same treatment. Thus, if the participant is in the intervention group they will receive L-PRF treatment on all of their ulcers. Eligible patients will be offered entry in the trial at the point where their clinician judges them suitable for treatment, i.e., when the lesion is clear of any debris or infection.

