### Data collection and management

#### Plans for assessment and collection of outcomes {18a}

Demographic data (age and sex), clinical data (number and size of ulcers), concurrent diseases will be collected for all consenting participants before randomisation (Fig. 1). Data on quality of life (QoL) will be collected fortnightly from first dressing change until discharge. Ulcers will be assessed twice weekly (see below) during the participant’s hospital stay, to a maximum of 70 days, and then again at a 6-month follow-up visit. Steps taken will be collected daily until 42 days (the point where cross-over may occur) or discharge, whichever comes first. Follow-up data collection at 6 months will require an outpatient appointment or a home visit (Fig. 3). Data, including photographs of ulcers, will be collected on electronic tablets using the Research Electronic Data Capture (REDCap) system by local researchers.

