#### Methods for additional analyses {20b}

##### Quality of life

Quality of life (QoL) will be analysed by calculating and comparing area under the curve (AUC) across intervention and controls. Baseline results will be triangulated with clinical observations to avoid bias and to determine how differences in healing rates correspond to differences in quality of life end-points.

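### EQ-5D collection stops at discharge, which healing may trigger, and resumes only at month 6, so the planned AUC comparison can misstate the quality-of-life effect; the first reading also appears to follow allocation

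*Protocol article*

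**What the plan says.** Outcomes {12} lists quality of life as a secondary end-point: "Generic quality of life (QoL) measured at first dressing change, fortnightly during in-patient stay and at 6-month follow-up". Plans for assessment and collection of outcomes {18a} agrees on when collection ends: "Data on quality of life (QoL) will be collected fortnightly from first dressing change until discharge". Neither section schedules a reading between discharge and month 6, and neither says that one is taken on the day of discharge. Outcomes {12} also notes that complete healing may lead to discharge.

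The Quality of life section gives the analysis: "Quality of life (QoL) will be analysed by calculating and comparing area under the curve (AUC) across intervention and controls". It states no time window, no rule for interpolating between readings and no covariates. Its next sentence refers to baseline results, which are to be set beside clinical observations.

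On timing, Trial design {8} says: "Consent (see ethics) and baseline data collection will precede randomisation". Section {18a} lists what is collected before randomisation (demographics, number and size of ulcers, concurrent diseases). EQ-5D is not in that list; it starts at the first dressing change. Allocated treatment is given at dressing changes: in the intervention arm, "blood will be collected twice per week at the time of dressing change". On blinding, Trial design {8} says: "Participants and practitioners will not be blinded, but the assessors will be completely blinded".

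**The concern.** The event that the trial hopes to bring forward also ends EQ-5D collection. Someone who heals on day 20 has readings on days 0 and 14 and then at month 6. Someone who heals on day 60 has readings on days 0, 14, 28, 42 and 56 and then at month 6. The healed period, where any gain lies, is represented mainly by one value at month 6, and the shape of the curve before it is interpolated over a gap whose length depends on the outcome and so differs by arm.

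The second issue is the status of the first reading. If it is taken at the first trial dressing change, an unblinded participant already knows the allocation, and a self-reported value can be affected by that knowledge. It is then a weak baseline, although the plan calls it one.

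At stake are the quality-of-life end-point and the data behind the link between healing and health-related quality of life in the Economic evaluation section. The two main end-points and the sample size are not affected.

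**Working it through.** **Healing rates.** Sample size {14} assumes 70% and 90% healed by day 42 with constant hazards.
- Control hazard: -ln(0.3)/42 = 0.02867 per day (mean 34.9 days).
- L-PRF hazard: -ln(0.1)/42 = 0.05482 per day (mean 18.2 days).
- Hazard ratio: ln(0.1)/ln(0.3) = 1.912.

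These are the plan's own inputs, since they reproduce its sample size: events = 4(1.960 + 0.842)²/(ln 1.912)² = 74.7; divided by the mean event probability 0.80 and by 2, this is 46.7, so 47 per group, as stated. The document gives no figure for quality of life.

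**Assumptions, not in the document.** Month 6 is day 182. AUC is trapezoidal to day 182. Readings fall on days 0, 14, 28 and so on while in hospital. Discharge is at healing, or at day 70 if unhealed. For the worked pair, utility is 0.6 before and 0.8 after healing.

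**Worked pair: healing on day 20 against day 60, utility stepping up at healing.**
- True: 0.2 × [(182 - 20) - (182 - 60)] = 0.2 × 40 = 8.0 utility-days.
- Schedule as written (last readings on days 14 and 56): 0.2 × [(182 - 14)/2 - (182 - 56)/2] = 0.2 × (84 - 63) = 4.2.
- With a discharge-day reading: 0.2 × [(6/2 + 162) - (4/2 + 122)] = 0.2 × 41 = 8.2.

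**Same pair, utility rising linearly from day 0 to healing.**
- True: 0.2 × [(182 - 10) - (182 - 30)] = 4.0.
- As written, day 20: 14 × 0.7/2 + 168 × 1.7/2 = 147.7. Day 60: 56 × 0.933/2 + 126 × 1.933/2 = 147.9. Difference: 0.2 × (-0.23) = -0.05.
- With a discharge-day reading the trapezoid is exact: 4.0.

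**Same pair, utility rising over the 28 days after discharge.**
- True: 0.2 × [(182 - 20 - 14) - (182 - 60 - 14)] = 8.0.
- As written: 4.2, as in the step case.
- With a discharge-day reading: 0.2 × [(182 - 20)/2 - (182 - 60)/2] = 0.2 × (81 - 61) = 4.0.

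**Arm level, step at healing, in days × utility gain.**
- True difference: (1/hazard) × (1 - e^(-182 × hazard)) is 34.70 for control and 18.24 for L-PRF; difference 16.46.
- Mean day of last reading: 14 × [S(14) + S(28) + S(42) + S(56)], where S(t) is the proportion unhealed at day t. Control: 14 × (0.669 + 0.448 + 0.300 + 0.201) = 22.66. L-PRF: 14 × (0.464 + 0.215 + 0.100 + 0.046) = 11.56.
- Recovered: (22.66 - 11.56)/2 = 5.55, plus 63 × 0.0054 = 0.34 for controls still unhealed at day 182, gives 5.89. Ratio 5.89/16.46 = 0.36.
- If every ulcer is taken as healed by day 70, the true difference is 30.20 - 17.85 = 12.35. Ratio 5.55/12.35 = 0.45.

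**Recovered share of the true arm difference.** The ranges cover three cases: healing continues after day 70 at the same hazard; the same, with all unhealed controls crossing over at day 42; and all ulcers healed by day 70.

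| Assumed path of utility | Schedule as written | Plus discharge-day EQ-5D |
|---|---|---|
| Step at healing | 0.36 to 0.45 | 0.95 to 1.16 |
| Linear rise up to healing | -0.9 to -1.8 | 1.00 to 1.11 |
| Rise over 28 days after discharge | 0.37 to 0.45 | 0.41 to 0.50 |

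If ulcers unhealed at day 70 never heal, the same calculation on the schedule as written gives 0.51 for the step, and the linear path shrinks to about 0.24 rather than reversing. Fortnightly EQ-5D to month 6, checked for the first two cases, recovers 0.97 (step), 0.86 to 0.90 (linear) and 1.00 (rise after discharge).

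**Baseline imbalance.** With 65 per arm and an assumed SD of 0.15 to 0.30, the standard error of the baseline difference is SD × √(2/65) = 0.026 to 0.053. Adjusting for a baseline correlated 0.5 with AUC leaves 1 - 0.5² = 0.75 of the variance.

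**The case against.** The case against has real weight. The trapezoid, its window and the utility paths are supplied here, and the Quality of life section fixes none of them. Interpolation rule, window and covariates commonly sit in a statistical analysis plan, which is not shown. The wording on fortnightly collection up to discharge does not exclude a reading on that day, and the schedule figure is missing. The economic model relates the primary end-point to health-related quality of life and does not take the arm-level AUC difference as input, so an error in the AUC does not pass straight into it. All of this stands, and it limits how firmly any size can be stated. It does not remove the gap: both sections that give the schedule leave discharge to month 6 empty, and an analysis plan cannot fill it with data.

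A reader might also infer that the plan compares AUC without baseline adjustment and is biased for that reason. The documents do not support this. The Quality of life section is silent on adjustment, and the stated preference for unadjusted results in Outcomes {12} concerns the two main end-points. In a randomised comparison, leaving out a baseline covariate costs precision; it does not itself cause bias.

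On timing, no section states the order of the first EQ-5D and disclosure of allocation. That it comes afterwards is the natural reading of {18a} with the intervention description, but it remains an inference.

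**Conclusion.** The concern holds in this form: EQ-5D collection depends on the outcome, and an AUC built on it can materially misstate the quality-of-life difference between arms. Under the assumptions listed, somewhat less than half of the difference is recovered if utility steps up at healing or rises only after discharge, and the sign can reverse if utility rises gradually up to healing.

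A reader might shorten this to a statement that the effect is halved. That is too strong: the factor depends on the path of utility, on whether a discharge-day reading is in fact taken, and on what happens to ulcers unhealed at day 70. The firm conclusion is that the result would rest on a part of the curve that is not measured.

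The timing of the first EQ-5D is a probable inconsistency with the statement that "baseline data collection will precede randomisation", to be settled against the schedule figures. Because the end-point is secondary, this should be corrected but does not threaten the main analyses.

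**What to change.** 1. Take the first EQ-5D with the other baseline data before randomisation, and say so in Outcomes {12} and {18a}.
2. Add one EQ-5D on the day of discharge. This repairs the step and gradual-rise cases (0.95 to 1.16) but not improvement that comes after discharge (0.41 to 0.50). For that, add at least one reading between discharge and month 6. The phones already supplied to participants make this feasible, with the same timing and mode in both arms.
3. Define AUC over the fixed 6 months from randomisation for everyone. An AUC limited to the inpatient stay would reward slower healing: with all ulcers taken as healed by day 70, the mean stay differs by 12.35 days, which at utility 0.6 is about 7.4 utility-days against the faster arm.
4. Compare arms by regressing AUC on arm and baseline EQ-5D, as a gain in precision.

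The cost is one or more five-item questionnaires per participant, an earlier time for the first, an amendment and some analysis-plan wording. Recruitment had begun when the article was written, so for participants already enrolled the first available value has to serve as baseline and any missing discharge readings cannot be recovered. Report this as a limitation.

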**Fig. 2 Fig2:**
[figure not shown]
‘Closed loop’ ulcer assessment process

Level of activity (step count) will be collected daily and monitored across both intervention and control groups until 42 days (the point where cross-over may occur) or discharge, whichever comes first—see analysis below.

#### Participant timeline {13}

See Fig. 1 for the participant’s timeline through the trial. Patients provide consent for randomisation when they have been confirmed to be eligible (including lesion free of debris and infection). See also ‘who will take informed consent’ above.

#### Sample size {14}

Sample size is based on the two primary outcomes: rate of healing and time to complete re-epithelialization. On the latter, we assume that 70% of ulcers will heal within 42 days with standard care [21]. Further, assuming that the intervention will increase this proportion to 90% and hazards are constant and proportional, for a two-sided test of the hazard ratio with a type I error of 5% and statistical power of 80% and a 1:1 allocation ratio, 47 individuals are required in each group. To allow for withdrawals and right censoring, we aim to recruit 65 patients in each group. We expect rate of healing to provide yet more precise estimates.

#### Recruitment {15}

Eligible individuals are identified by the clinical research team and invited to participate by the local research fellow (see eligibility criteria).

### Assignment of intervention: allocation

#### Sequence generation, concealment mechanism and implementation {16a, 16b, 16c}

Participants will be enrolled sequentially and randomly allocated (1:1) to undergo L-PRF treatment or usual care using a ‘digital sealed envelope’ method [22]. An allocation table will be generated remotely by the trial statistician at The University of Birmingham to allocate participants in a 1:1 ratio at the level of the individual over the course of the trial. A random number generator will be used to generate a random sequence of the numbers between 1 to N inclusive. A permuted block randomisation method will be used by randomly selecting blocks of size 2, 4, 6 or 8 in order to maintain balance between the numbers allocated to each of the two groups. The generated table will be uploaded into the REDCap software to be used for participant enrolment. Access to the allocation table will be restricted. When a participant’s details are submitted, the trial arm and a unique study number will be assigned and revealed to the local clinician so that the randomised group that the participant is assigned to cannot be altered.

### Assignment of interventions: blinding

#### Who will be blinded {17a}

The Nepal research team, the database managers in Birmingham, the clinical staff carrying out dressing changes in the room designated for this purpose and participants themselves will be aware of participants’ randomly assigned group. Ward staff will not be informed. Researchers in Birmingham involved in the data analyses will be blinded to treatment allocation (Fig. 2).

#### Procedure for unblinding {17b}

There is no requirement for an emergency unblinding procedure.

### Data collection and management

#### Plans for assessment and collection of outcomes {18a}

Demographic data (age and sex), clinical data (number and size of ulcers), concurrent diseases will be collected for all consenting participants before randomisation (Fig. 1). Data on quality of life (QoL) will be collected fortnightly from first dressing change until discharge. Ulcers will be assessed twice weekly (see below) during the participant’s hospital stay, to a maximum of 70 days, and then again at a 6-month follow-up visit. Steps taken will be collected daily until 42 days (the point where cross-over may occur) or discharge, whichever comes first. Follow-up data collection at 6 months will require an outpatient appointment or a home visit (Fig. 3). Data, including photographs of ulcers, will be collected on electronic tablets using the Research Electronic Data Capture (REDCap) system by local researchers.

**Fig. 3 Fig3:**
[figure not shown]
Schedule of enrolment, intervention and assessment

### Ulcer measurements

Standardised photographs [23] will be taken twice weekly during inpatient stay dressing changes for participants in both intervention and control groups. Photographs will be obtained in Nepal using two different methods (Fig. 4). The photographs will be transferred to the University of Birmingham and the ulcer dimensions measured in three ways. Two observers will be trained to take these measurements. Both observers will be blinded to the participant’s allocated treatment. All photographs from a given participant will be assigned to the observers at random, separately for the two methods of photography. So that the measurements are not all relegated to the end of the study, they will be made in batches of ten participants reaching completion of their baseline treatments (at complete re-epithelization or 70 days from randomisation). A proportion (20%) of all ulcer photographs will be measured by both observers to test inter-rater reliability. These photographs will be selected at random.

**Fig. 4 Fig4:**
[figure not shown]
Ulcer capture and measurement process

The date at which complete re-epithelization took place will be determined by the local clinician. Photographs will be taken at the point of complete re-epithelialization and during the follow-up visit.

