##### Measurements

The above analyses of healing rate and time of complete re-epithelialisation will be made separately for each method of measurement. Photographs will be assessed blind to allocated treatment by two trained observers at the University of Birmingham (Fig. 2). Inter-rater reliability of the measurements will be made on 20% of ulcer photographs and assessed using interclass correlation coefficients.

Measurements are based on the ARANZ ® and tablet-based cameras (see Fig. 2). The ARANZ® images are measured in two ways: (1) manual tracings and (2) automatic tracings of wounds using a camera specifically designed to obtain standardised photographs of ulcers for scientific purposes. The distance of the camera from the ulcer surface is controlled by triangulation of three laser lights. The images taken by the camera in the tablet are calibrated digitally by reference to a measurement ruler in the frame. The areas (cm^2^) are then generated within the different software packages. We will measure, agreement between the methods of measurement:
The Push tool vs. the automated ARANZ® methodThe automated vs. manual ARANZ® method

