## Discussion

This protocol describes an individually randomised control trial to evaluate a treatment using autologous blood products L-PRF, to promote ulcer healing in leprosy. Despite the promising anecdotal evidence regarding this treatment, high-quality, empirical data are currently unavailable [12, 14].

Most of the evidence on ulcer healing, including the Cochrane review [12], is based on proportion of ulcers healed (completely epithelialized) by 42 days. This is sub-optimal because complete epithelialisation is a clinical decision that is also used to decide on discharge. This provides an opportunity for observer (outcome) bias. For this reason, we will measure rate of healing. These measures are all made centrally (in Birmingham) by two observers who are ‘blind’ to intervention status.

Activity measurements are not a primary outcome measure in our study. However, by collecting step-count daily and over the course of the inpatient stay over the periods specified above, we can exclude activity as a confounding factor in any differences found in ulcer healing rates between intervention and control groups.

We are also planning to do a range of nested studies. Given sufficient time and resources, we hope to video tape a subset of dressing changes (five intervention and two controls selected at random in Birmingham) as a means of photograph supervision and for additional quality control. We will also develop a more detailed health economics protocol. Finally, we will develop follow on studies based on the results of the trial.

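### The protocol gives two incompatible sources for the event date of co-primary time to complete re-epithelialization: an unblinded local clinician, and three blinded photographic methods

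*Protocol article*

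**What the plan says.** Outcomes {12} lists two main end-points: rate of healing, and time to complete re-epithelialization right-censored at 42 days. Sample size {14} names both but calculates only for the second.

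The protocol describes the source of the healing date in two ways.

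- **Clinician.** The text after Fig. 4, under Ulcer measurements, states: "The date at which complete re-epithelization took place will be determined by the local clinician". Sequence generation {16a, 16b, 16c} says that "the trial arm and a unique study number will be assigned and revealed to the local clinician". Trial design {8} says: "Participants and practitioners will not be blinded, but the assessors will be completely blinded". Who will be blinded {17a} lists among those aware of allocation: "The Nepal research team, the database managers in Birmingham, the clinical staff carrying out dressing changes in the room designated for this purpose".
- **Photographs.** The Measurements subsection states: "The above analyses of healing rate and time of complete re-epithelialisation will be made separately for each method of measurement". The Discussion also says that three methods measure both healing rate and time to healing. Statistical methods {20a} counts the primary tests as two outcomes, adjusted and unadjusted, for three types of ulcer assessment.

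The Discussion describes complete epithelialisation as a clinical decision also used for discharge, and adds: "This provides an opportunity for observer (outcome) bias". Its answer is to measure rate of healing as well. Outcomes {12} adds one check: "we will monitor for cases discharged before the blinded assessor in Birmingham has noted complete re-epithelization". It attaches no analysis rule to that check.

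**The concern.** The Cox model needs one event date per participant, and the protocol does not settle which one. If it is the clinician's, a judgement made with knowledge of the arm feeds straight into the hazard ratio, and a positive result could not be separated from earlier calling of healing in the L-PRF arm. The same judgement may trigger discharge and so end the inpatient photograph series. The end-point can also, on its own, meet the interim threshold, which applies to either main end-point (Interim analyses {21b}). If the choice of date is left until allocation-labelled results are visible, it becomes data-driven.

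**Working it through.** **1. Does the sizing rest on this end-point?** Inputs from Sample size {14}: 70% and 90% healed by 42 days, constant proportional hazards, two-sided 5%, 80% power, 1:1.

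- HR = ln(1 − 0.90) / ln(1 − 0.70) = ln 0.1 / ln 0.3 = 1.912.
- Events (Schoenfeld) = 4 × (1.960 + 0.842)² / (ln 1.912)² = 74.67, rounded up to 75.
- Mean event probability = (0.70 + 0.90) / 2 = 0.80; 75 / 0.80 = 93.75 participants, so 47 per group.

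This reproduces the stated 47 exactly, from the healing proportions alone. Changing who dates the event would not alter it.

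**2. Are the two descriptions compatible?**

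- Photograph-based date: 2 outcomes × 2 (adjusted, unadjusted) × 3 methods = 12 tests, as Statistical methods {20a} counts them.
- Clinician's date: rate of healing gives 1 × 2 × 3 = 6. Time to healing gives 1 × 2 × 1 = 2, because one date per participant does not vary by photographic method. The total is 8 distinct tests.

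So the stated family of 12 fits only the photographic definition, while the sentence after Fig. 4 fits only the clinician's. A permutation stepdown is not distorted by exact duplicates, so the miscount does not itself cost error control. It shows that the end-point is defined in two ways.

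**3. How much could an unblinded date matter?** The documents give no figure for early calling, so this part is illustrative. Assumptions: no true effect, 65 per arm, 70% healed by day 42 in both arms, visits every 3.5 days (twice weekly), log-rank test, and early calling in the L-PRF arm only.

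| L-PRF ulcers called early | Constant hazards, two-sided 5% | Lognormal times, one-sided 2.5% (SD of log time 0.8 to 0.4) |
|---|---|---|
| None | 5.6% | nominal 2.5% |
| Half, by one visit | 5.9% | up to about 9% |
| All, by one visit | 9.0% | 12% to 24% |
| Half, by two visits | 8.7% | not tabulated |
| All, by two visits | 22.5% | 32% to 71% |

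Constant hazards is the protocol's own sizing assumption. The lognormal columns show how far the answer depends on the spread of healing times: the tighter the spread, the more a shift of a few days matters. Once bias pushes in one direction, almost all rejections fall on that side, so the two columns are comparable in the lower rows. They are not comparable in the first row.

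**The case against.** A reader might infer that the end-point simply is unblinded. The documents do not settle that. Three places (Statistical methods {20a}, Measurements, Discussion) fit a blinded, photograph-based event time, and the sentence after Fig. 4 could be read as recording when the clinician declares healing, which prompts the closing photograph. What is established is a contradiction, with bias following on one of its two readings.

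A reader might also infer that the protocol claims to have removed observer bias from this end-point. It does not. The Discussion admits the bias and answers it by adding rate of healing, read centrally and blind. That mitigation is real: one co-primary is protected, and the Discussion promises to report differing results openly. It does nothing for the other co-primary.

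Nor does the check on discharges fail because photographs are read late ("they will be made in batches of ten participants reaching completion of their baseline treatments"). The protocol promises monitoring, not confirmation before discharge, and batch reading can still reveal disagreement during the trial. The weakness is that nothing follows from a disagreement once it is found.

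Finally, the larger false-positive rates require every L-PRF ulcer, and no control ulcer, to be called early. Partial misdating by one visit is close to nominal under constant hazards. That objection stands, and it limits the size claimed, not the contradiction.

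**Conclusion.** The point holds as a contradiction in the definition of a co-primary end-point, the one for which the trial's 47 per group was calculated. If the clinician's date governs, the end-point carries the bias that the Discussion names, and three of the planned analyses collapse into one. If the photographs govern, the sentence after Fig. 4 does not define the end-point and must say so.

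The false-positive rate could be barely above nominal (half of L-PRF ulcers called one visit early, constant hazards), about 9% to 24% (all, one visit), or about 22% to 71% (all, two visits). These ranges mix a two-sided 5% test at the lower end with a one-sided 2.5% test at the upper end, and they rest on assumed early calling and an assumed distribution of healing times. No single figure should be quoted as the bias of this trial.

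**What to change.** Reconcile Outcomes {12}, the text after Fig. 4, Statistical methods {20a}, Measurements and the Discussion, before any analysis by arm:

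1. Define the primary event date as the date of the first photograph that a blinded Birmingham observer reads as completely re-epithelialized, by one named method. Include the photograph taken when the clinician declares healing.
2. Keep the clinician's date as a sensitivity analysis, and report clinician–photograph disagreement by arm.
3. For cases the clinician declares healed but the blinded reading does not confirm, do not censor at the last photograph as if that were non-informative. These ulcers are probably close to healed, and the unblinded call may itself have ended the series through discharge. Report the result twice: counted as healed at the clinician's date, and counted as unhealed to day 42.
4. State the multiplicity family that follows from the chosen definition.

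The cost is wording, since the photographs and blinded readers are already planned. The downside is that a photographic reading is slightly less certain than bedside inspection, and some cases will be discordant; the documents do not allow their number to be estimated.
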